#### The standardised usual care intervention

Participants allocated to receive standardised usual care are provided with all the information given to those allocated to use the EDGE platform, but without the use of a tablet computer or the facility for daily monitoring of symptoms and physiological variables. The research nurse provides participants with leaflets based on those currently produced by the Oxfordshire Community Respiratory service. Personalised information intended to help patients understand their condition includes information about how to use their medications and when they should be used, a self-management plan with written guidelines on what to do and whom to contact if they experience an exacerbation and dietary advice is provided. If the participant has not attended a pulmonary rehabilitation course they are invited to do so.

### Outcomes

Trial outcome measures will be recorded as indicated in table 1.

**Table 1 BMJOPEN2013004437TB1:** Trial outcome measures

	Baseline assessment visit	3 months	6 months	12 months
Primary outcome				
SGRQ-C (quality of life)^18^	x		x	x
Secondary outcomes				
Number of exacerbations	x	x	x	x
Time to first exacerbation (days)		x	x	x
Unplanned healthcare contacts		x	x	x
EuroQol 5 Dimension Questionnaire^22^	x		x	x
Self-completed 20 item depression measure D^20^	x		x	x
Self-completed 10 item anxiety measure^21^	x		x	x
Beliefs about Medicines Questionnaire^19^	x		x	x
Medication adherence report schedule^19^	x		x	x
Prescribed medicines	x	x	x	x
Smoking status	x		x	x
Health service usage	x	x	x	x
Death		x	x	x
Admission to hospital	x	x	x	x
Days out hospital	x	x	x	x

SGRQ-C, St George's Respiratory Questionnaire for COPD patients.

#### Primary outcome measure

The primary outcome is the SGRQ-C^8^
^18^ used to assess quality of life in patients with moderate to severe COPD.

#### Secondary outcome measures

The following secondary endpoints will be used to evaluate the impact of the intervention in comparison with usual care (1) impact on hospital admissions (number of admissions and days out of hospital) and deaths; (2) the number of recorded exacerbations defined as episodes in which antibiotics or oral steroids were prescribed or in which the patients were seen in the accident and emergency department and/or admitted to hospital as a result of a respiratory episode; (3) time to first exacerbation; (4) beliefs about respiratory medicine use measured with the Beliefs about Medicines Questionnaire;^9^
^19^ (5) self-reported medication use measured with the Medication Adherence Report Schedule;^10^
^11^
^19^ (6) self-reported smoking cessation; (7) mood measured with the Standard Checklist 20-item Questionnaire (SCL-20) for depression^20^ and the Standard Checklist 10-item Anxiety Measure (SCL-10A)^21^ and (8) health status measured with the EuroQol 5-Dimension Questionnaire (EQ-5D).^22^

Details of number and duration of hospital admissions will be measured by self-report and confirmed where possible by a review of hospital discharge letters and central hospital admissions data. Records of deaths will be obtained from general practices and further details will be obtained, where necessary, from hospital records.

Details of exacerbations of COPD will be recorded on a record form held by all participants. This will include number, severity, medications prescribed and outcomes to enable, where possible, details to be confirmed by review of medical records or, if deterioration results in admission, review of hospital records.

Costs of healthcare will be identified using a brief questionnaire to obtain self-reported information about visits to general practitioners. Standard costs will be used for hospital admissions and prescribed respiratory medicine.

### Sample size

The sample size calculations are based on the number of patients required to demonstrate a mean difference of 6.6 on the St George's Respiratory Questionnaire between the two trial groups to which participants are allocated, over a 12-month period (equivalent to 7.3 on SGRQ-C).^18^ Although there is limited data on this outcome in settings using computer-based interventions, we have estimated the SD at 12.7 based on a study using the SGRQ-C.^23^ A trial using these estimates with a power of 90% and significance level of 0.05 (2-sided), with 2:1 allocation between intervention and usual care and allowing for 10% loss to follow-up would require 165 patients.

We also have 98% power to identify the difference in admissions to hospital at 3 months based on effect sizes of previous intensive interventions with this group of patients^24^ and 52% power to detect the difference in admissions at 12 months based on a systematic review of interventions in COPD.^25^ In both cases, a 5% loss to follow-up has been assumed.

### Randomisation

Participants are randomised with an allocation ratio of 2:1 intervention to usual care using Sortition V.1.2 (an online, web-based randomisation system developed by the Primary Care Clinical Trials Unit at the University of Oxford). A computer schedule based on recruiting site (Oxfordshire or Berkshire), age (≤70 years or >70 years), gender, COPD severity (moderate or severe/very severe) and current smoking status (yes or no) is used to minimise imbalance between the groups,^26^ and is monitored by an independent statistician. The research nurse randomises the patient by accessing Sortition using a web-browser on a tablet computer at the assessment visit only after completion of consent procedures and baseline measurements, including completion of the SGRQ-C.

Self-completed outcome measures at 6 and 12 months are completed without guidance by the research team and prior to any further assessment or discussion of clinical care. Research and clinical teams are trained in the potential for measures to be biased by their interactions with participants. A record of all contacts with trial participants is kept to examine potential for interactions with patients not specified in the trial protocol.

### Trial procedures

#### Recruitment

Potentially eligible patients are identified from those discharged from hospital following a COPD-related admission, from respiratory hospital outpatient clinics, pulmonary rehabilitation courses and from primary care clinics, and are sent an invitation to participate in the trial. The invitation includes a patient information booklet, a reply slip and prepaid envelope. Patients interested in participating are asked to return their reply slips by post to the research team. The research nurse then contacts the patient by telephone to arrange an initial assessment visit. At this visit eligibility is confirmed, written informed consent is obtained and baseline data are collected for those consenting to participate.

All participants are assessed at baseline by a healthcare professional and complete self-completed measures prior to randomisation and intervention allocation. The use of medication by participants is recorded at the baseline and follow-up assessment visits. Information collected includes type, dose and frequency of COPD medication (tablets and inhalers) as well as a list of other medication taken. A detailed smoking history is taken at the baseline assessment visit; self-reported smoking status is recorded at subsequent assessments.

#### Patient follow-up and retention

Patients remain in the trial for 12 months with assessments at a baseline visit, 3, 6 and 12 months. The primary outcome measure is collected at baseline, and 6 and 12 months after randomisation. Secondary outcome measures are collected at baseline, 3, 6 and 12 months.

The 3-month assessment is a telephone contact with patients sent reminders prior to the assessment date. For patients allocated to standardised usual care, a reminder is posted prior to the assessment date. For patients receiving the EDGE platform intervention, this reminder is sent in the form of a message to the tablet computer. The 6 and 12 months visits are carried out either at home or at clinic, with patients receiving postal or electronic reminders prior to the assessment visit date. The researcher ensures at each visit that all outcome measures are complete to ensure maximal follow-up data are collected.

All patients have the right to withdraw from the trial at any point, without providing a reason. Those patients who do withdraw from the trial will be asked if they would be willing to provide follow-up information at the 6 and 12 months assessment points. If patients decline, no further information will be collected.

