#### The EDGE platform-based intervention

Participants allocated to receive the Internet-linked tablet computer (EDGE platform)-based intervention are provided with an Android tablet computer (Samsung Galaxy Tab) running the application software and Bluetooth-enabled oximeter probe (Nonin, PureSAT, 956OBT, Nonin Medical Inc, Plymouth, Minnesota, USA). Participants are briefly instructed on the use of the EDGE platform by the research nurse and are provided with a brief information booklet giving details of its use. Participants continue to input their symptom data and clinical recordings daily throughout the duration of the trial. Patients are informed that the EDGE system is not a replacement for their usual clinical care, and that in the event of deterioration in their health they should contact their general practitioner or community respiratory nurse as usual. However, data are reviewed by a clinician at no less than 4-day intervals, and changes in heart rate, oxygen saturation or symptom score that cross the participant's specific threshold for that parameter and persist for more than 4 days are followed up with a phone call to either the patient, general practitioner or community respiratory nurse as appropriate. If depression or anxiety scores equal or exceed a threshold of 10, then the general practitioner is informed by letter.

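### The withdrawal rule uses one question to cover both visits and records, so a patient who declines is also lost to record-based follow-up for deaths and admissions

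*Protocol article*

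**What the plan says.** The rule is in the Protocol article, *Patient follow-up and retention*. Patients may withdraw at any time without a reason. Those who do are "asked if they would be willing to provide follow-up information at the 6 and 12 months assessment points". The next sentence is: "If patients decline, no further information will be collected". No separate question about medical records is described.

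*Secondary outcome measures* lists "impact on hospital admissions (number of admissions and days out of hospital) and deaths" among the endpoints and gives their sources:

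- **Deaths:** "Records of deaths will be obtained from general practices and further details will be obtained, where necessary, from hospital records".
- **Admissions:** "Details of number and duration of hospital admissions will be measured by self-report and confirmed where possible by a review of hospital discharge letters", and also by central hospital admissions data.
- **Exacerbations:** entered on a form that the participant holds, with confirmation from medical or hospital records where possible. The definition rests on prescriptions of antibiotics or oral steroids, emergency department attendance and admission.

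Table 1 schedules deaths and admissions at 3, 6 and 12 months. *Sample size* states power for admissions at 3 months (98%) and at 12 months (52%), and adds: "In both cases, a 5% loss to follow-up has been assumed". The allowance for SGRQ-C is 10%. *Statistical methods* specifies intention-to-treat for the principal comparisons.

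**The concern.** Declining to give further information at assessment points is a different decision from refusing review of one's records. The rule joins the two, so a patient who is tired of questionnaires leaves the mortality and admissions data as completely as one who wants no further involvement. Deaths are record-sourced by design, so that loss is avoidable. Admissions are avoidable in part, since the records now used for confirmation could still show them.

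Events that were never collected cannot be recovered at analysis. The sensitivity analyses that the article plans can only vary assumptions about them. This fits poorly with an intention-to-treat comparison and with the stated aim of using morbidity, mortality and admission data to design later evaluations.

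The offer also starts at 6 months. A patient who withdraws at week 4 is not asked for the 3-month contact. If that patient accepts the later assessments, early events may still be reported in retrospect. If the patient declines, they are not collected.

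**Working it through.** **1. The number randomised.** Inputs from *Sample size*: difference 7.3 on SGRQ-C, SD 12.7, power 90%, two-sided 0.05, allocation 2:1, loss 10%, stated total 165.

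- Normal approximation, smaller arm: 1.5 × (12.7 × (1.960 + 1.282) / 7.3)² = 47.7, so 48 + 96 = 144, and 144 / 0.9 = 160.
- Noncentral t: 49 + 98 = 147. Inflating the smaller arm, 49 / 0.9 = 54.4, rounded up to 55. At 2:1 this is 55 + 110 = 165.

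The stated 165 is reproduced, with 110 EDGE and 55 usual care. The 98% and 52% powers for admissions cannot be checked, because no admission rates are given.

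**2. The largest number affected.**

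- At the 5% assumed for admissions: 165 × 0.05 = 8.25 (5.5 + 2.75 if equal by arm).
- At the 10% allowed for SGRQ-C: 165 × 0.10 = 16.5 (11 + 5.5).

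Both are ceilings. They count loss for any reason, whereas the rule applies only to those who withdraw and then decline. Patients lost in other ways are not barred from record review.

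**3. The rule beside the two loss allowances.** At 12 months the plan expects 165 × 0.95 = 156.75 patients with admissions data and 165 × 0.90 = 148.5 with SGRQ-C. About 8 patients are thus expected to supply admissions without a questionnaire. The article does not say how. Records are the obvious route, and the rule closes it for withdrawers who decline.

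**4. When bias would follow.** This step is an illustration on assumed values. Let the true risk be equal in both arms, let a fraction w be lost, and let those lost have r times the risk of those retained. The true risk p then equals q × (1 − w + w × r), where q is the risk observed among the retained. The observed risk ratio, EDGE to usual care, is

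(1 + w_UC × (r − 1)) / (1 + w_EDGE × (r − 1)).

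| Loss, EDGE v usual care | Patients lost | r = 1 | r = 1.5 | r = 2 |
|---|---|---|---|---|
| 10% v 10% | 16.5 | 1.00 | 1.00 | 1.00 |
| 6% v 3% | 8.25 | 1.00 | 0.985 | 0.972 |
| 12.5% v 5% | 16.5 | 1.00 | 0.965 | 0.933 |
| 15% v 0% | 16.5 | 1.00 | 0.930 | 0.870 |

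Example: 12.5% v 5% with r = 2 gives 1.05 / 1.125 = 0.933. If the imbalance or the risk relation is reversed, the ratio moves above 1.

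For scale, assume a 40% risk with 110 and 55 patients. The standard error of the log risk ratio is √(0.6 / 44 + 0.6 / 22) = 0.202. The 6% v 3% row shifts the log ratio by 0.015 to 0.029, or 0.07 to 0.14 standard errors. The 12.5% v 5% row shifts it by 0.036 to 0.069, or 0.18 to 0.34 standard errors.

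The formula discards each lost patient completely. The article does not say that events before withdrawal are discarded, so these shifts are overstated if those events are kept.

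**The case against.** The best defence has four parts.

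- **Refusal must be respected.** Follow-up information could be read to include permission to use records, in which case stopping after a refusal is correct. Respect for refusal stands, but it does not justify putting one question where patients may hold two different wishes.
- **Detail may sit elsewhere.** Levels of withdrawal and consent to record access often belong to a full protocol or consent form, and neither is shown. This would answer a complaint that graded options are missing. It does not answer a rule that the article states outright and that, as worded, ends all collection.
- **Little is at stake.** The endpoints are secondary, the article admits low power for admission rates, and SGRQ-C cannot come from records. All of this stands and limits the weight of the point.
- **Missing data are addressed.** The mechanism is to be investigated and sensitivity analyses are planned. That stands, but neither supplies the events.

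A reader might infer more than the document supports. Only EDGE patients have a daily task ("Participants continue to input their symptom data and clinical recordings daily throughout the duration of the trial"), so one could conclude that EDGE loses more patients, that they are sicker, and that the comparison favours EDGE. No withdrawal rate by arm and no risk among withdrawers is given. Over 80% of the earlier cohort used the tablet daily, and usual-care patients in an open trial may leave too. Nor does the article say that stopping the tablet counts as withdrawal. Finally, it would be wrong to say that admissions come without patient effort: they are self-reported first and confirmed from records where possible. Only deaths are record-sourced by design.

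**Conclusion.** The point holds in a limited form. As worded, the rule ends record-based follow-up together with assessments, and the offer leaves out the 3-month point. The avoidable loss is chiefly deaths, and admissions as far as records hold them.

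The ceiling is about 8 of 165 patients at the admissions allowance. The figure of 16 to 17 belongs to the SGRQ-C allowance and should not be read as the expected loss of deaths and admissions. The actual number is lower than either ceiling to the extent that patients are lost for reasons other than withdrawing and declining.

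Bias in the intention-to-treat comparison is possible only if withdrawal differs by arm, in rate or in who leaves, and withdrawers differ in risk from those who stay. The document establishes neither, so no direction can be claimed. The primary outcome is untouched. The conclusion rests on a literal reading of the sentence and on the unseen consent form not already providing for record review after withdrawal.

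**What to change.** When a patient withdraws, ask two separate questions:

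- (a) whether the patient will complete the remaining assessments, including the 3-month contact if it is still due;
- (b) whether general practice and hospital records may be reviewed for deaths, admissions and exacerbation prescriptions up to 12 months.

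Record both answers with the date, and stop all collection only if both are refused.

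The cost is an amendment to the withdrawal form, and to the consent form if that does not already cover record review after withdrawal. In the latter case patients already enrolled would need to be told. The record sources are ones that the trial already uses.

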### Statistical methods

The principal comparisons will be performed on an intention-to-treat basis. The trial results will be presented as comparative summary statistics (difference in response rates or means) with 95% CI. If appropriate, and depending on the distribution of the continuous outcome measures, a linear mixed-effects model will be used to analyse SGRQ-C over the 12-month period of the trial, adjusting for baseline value and minimisation covariates. Treatment-time interaction will be included in the model to assess the treatment effect at 12 months. We will formally assess the distribution of the change from baseline for evidence of departure from normality. If necessary, data will be either transformed or analysed using a non-parametric equivalent. The nature and mechanism for the missing outcomes will be investigated, though mixed-effects model implicitly account for data missing at random. Sensitivity analyses will be carried out to examine the robustness of the results with different assumptions about departures from randomisation policies, and handling of missing data. Binary outcomes will be analysed using log-binomial regression, adjusting for covariates as described above.

The intervention effect will be assessed by analysis of subgroups defined by severity of COPD, smoking status, hospital admission in the previous year, attendance on a pulmonary rehabilitation course in the previous year and the presence or absence of live-in support. The full detailed statistical analysis plan, including any prespecified subgroup and sensitivity analyses, will be prepared before the final analysis by the trial statistician.

### Embedded qualitative process evaluation

An embedded qualitative study will involve individual interviews with a subgroup of up to 30 patients in the intervention group invited to take part. Interviews will take place at baseline (after patients have been randomised and prior to the delivery of the EDGE platform-based intervention) and after the 12-month visit, and will be carried out by a qualitative researcher. The aim of the baseline interview is to explore patients’ current self-management strategies, while the second interview will focus on how the EDGE platform intervention has impacted on their self-management of COPD and explore issues of acceptability, everyday use and usability.

A maximum variation sample in terms of age, gender, employment status, care support, severity of COPD, exacerbation frequency and experience of using computer or smart phone technology will be sought. Interviews will be audio-recorded and transcribed verbatim. NVivo will be used to facilitate organisation and analysis of data. Analytical procedures will follow grounded theory methods,^27^ including double coding by a second qualitative researcher to ensure rigour. The EDGE COPD trial will be carried out in conformance with the principles of the current version of the Declaration of Helsinki and the other regulations in force.

## Discussion

This trial is designed to assess the extent to which a telehealth platform designed to support self-management improves quality of life for people with COPD. Reduced quality of life is an important aspect of COPD that has been shown to be responsive to group and one-to-one interventions.^7^ This trial is powered to show a clinically important effect and provide data from which to design further trials to explore cost-effectiveness and potential reduction in hospital admissions.

The trial intervention uses a novel implementation of telehealth using a non-proprietary tablet computer designed to be integrated into day-to-day life and clinical care. In addition to being non-obtrusive, it provides, at relatively low cost, in relation to previous telehealth systems, facilities for monitoring, communication, self-management support and education delivery. The development of the system was carried out iteratively using best practice to involve patients, engineers and clinicians in repeated testing and assessment.^28^

The underlying approach in implementing telehealth within this trial is to provide a system focused around the needs of the patient with collection of data that can be analysed over a period of time and used to inform future management. Although future implementations of this system may allow real-time alerts to inform management, consistent experience to date with existing commercial telehealth systems has been that the high rates of false-positive alerts have been unacceptable to clinicians and patients. This trial will provide data to evaluate the potential of the patient-specific tailored alerts available in the system for implementation in practice.

The current evaluation has a number of strengths in comparison with previous trials of telehealth systems. In particular, the information provided by the platform is timely, and immediately available, but does not provide an overwhelming flow of data. The platform has been evaluated for acceptability and feasibility in a cohort study over a period of 6 months in which the tablets were used daily by over 80% of participants. The process of completing diaries and measuring oxygen saturation takes less than 3 min, with an average of five video segments viewed by each participant during their 6-month participation in the cohort study. A qualitative process evaluation adds to the strength of the design. The unbalanced allocation will provide additional power to examine the effect of the EDGE platform across a wide range of participants. The trial, however, is not sufficiently large to provide a detailed cost-effectiveness evaluation, or to provide sufficient power to demonstrate clinically important differences between intervention and usual care groups for hospital admission rates. The trial is due to report in September 2015.
